## Abstract

**Background:**

Fun For Wellness (FFW) is an online behavioral intervention designed to promote growth in well-being and physical activity by providing capability-enhancing learning opportunities to participants. The conceptual framework for the FFW intervention is guided by self-efficacy theory. Evidence has been provided for the efficacy of FFW to promote self-reported free-living physical well-being actions in adults who comply with the intervention. The objective of this manuscript is to describe the protocol for a feasibility study designed to address uncertainties regarding the inclusion of accelerometer-based assessment of free-living physical activity within the FFW online intervention among adults with obesity in the United States of America (USA).

**Method:**

The study design is a prospective, double-blind, parallel group randomized pilot trial. Thirty participants will be randomly assigned to the FFW or usual care (UC) group to achieve a 1:1 group (i.e., FFW:UC) assignment. Recruitment of participants is scheduled to begin on 29 April 2019 at a local bariatric services center within a major healthcare organization in the Midwest of the USA. There are five eligibility criteria for participation in this study: (1) between 18 and 64 years old, (2) a body mass index ≥ 25.00 kg/m^2^, (3) ability to access the online intervention, (4) the absence of simultaneous enrollment in another intervention program promoting physical activity, and (5) willingness to comply with instructions for physical activity monitoring. Eligibility verification and data collection will be conducted online. Three waves of data will be collected over a 13-week period. Instruments designed to measure demographic information, anthropometric characteristics, acceptability and feasibility of accelerometer-based assessment of physical activity, self-efficacy, and well-being will be included in the study. Data will be analyzed using descriptive statistics (e.g., recruitment rates), Pearson’s correlation coefficient, Bland-Altman analyses, and inferential statistical models under both an intent to treat approach and a complier average causal effect approach.

**Discussion:**

Results are intended to inform the preparation of a future definitive randomized controlled trial.

**Trial registration:**

ClinicalTrials.gov, NCT03906942, registered 8 April 2019.

**Electronic supplementary material:**

The online version of this article (10.1186/s40814-019-0455-0) contains supplementary material, which is available to authorized users.

The World Health Organization (WHO) estimates that there are 650 million adults with obesity and that the number of adults with obesity has tripled since 1975 [1]. Obesity is a risk factor for major non-communicable diseases such as cardiovascular disease, type II diabetes, musculoskeletal disorders, and some cancers [2]. To reduce the prevalence of adults with obesity, the WHO recommends that individuals limit energy intake from low-quality food sources (e.g., highly processed foods high in fat), increase energy intake from high-quality food sources (e.g., raw vegetables), and engage in a recommended amount of physical activity for health [1]. Examples of a recommended amount of physical activity (counting only those physical activities that you do for at least 10 min at a time) for adults include at least 150 min per week of moderate physical activity, at least 75 min per week of vigorous physical activity, or an equivalent combination of the two recommendations listed above [3, 4]. There is evidence, however, that very few (e.g., < 5%) adults with obesity may engage in a recommended amount of physical activity [5]. Fortunately, there also is evidence that well-designed cognitive-behavioral interventions can successfully promote physical activity in obese adults [6].

## Self-efficacy theory

Self-efficacy theory resides within the more general social cognitive theory [7]. In social cognitive theory, individuals are regarded as proactive agents in the regulation of their cognition, motivation, actions, and emotions. Self-efficacy judgments occupy a central role in self-efficacy theory and are defined as domain-specific beliefs held by individuals about their ability to successfully execute differing levels of performance given certain situational demands [8]. The formation of self-efficacy beliefs is believed to rely upon the cognitive processing of diverse sources of efficacy information that can be categorized as follows: past performance accomplishments, vicarious experiences, verbal persuasion, and physiological and/or emotional states. Two proposed outcomes of self-efficacy beliefs are an individual’s thought patterns (e.g., goal setting, worry, and attributions) and behavior (e.g., challenges undertaken, effort expended on challenges undertaken, and persistence in the face of difficulties that arise during challenges undertaken). A necessary condition for valid testing of self-efficacy theory is concordance between the domain-specific self-efficacy beliefs and the proposed outcomes of the self-efficacy beliefs of interest [8]. There is a rich literature on the potential importance of increasing self-efficacy for physical activity as a mechanism for promoting physical activity in adults [9, 10].

### Physical activity

Physical activity has been defined as bodily movement produced by skeletal muscles that require energy expenditure [11]. There is evidence that insufficient physical activity increases the risk of several major non-communicable diseases (e.g., cardiovascular disease, type II diabetes, and some cancers) in adults worldwide [12]. Unfortunately, insufficient physical activity in the adult population is a global pandemic [13, 14]. Successfully addressing this pandemic will require ongoing and wide implementation of a variety of intervention strategies (e.g., community-wide, informational, behavioral, social, policy, and built environment) at multiple levels of society (e.g., individual, neighborhood, municipality, country) across the globe [15, 16]. At the individual-level, there is evidence that behavioral interventions designed to promote physical activity by focusing on personal psychological attributes (e.g., self-efficacy beliefs) can be effective [9, 10]. Delivering a physical activity intervention online has been shown to be an effective mode of delivery [17, 18] that also may allow for efficient scaling up of an intervention [16]. Thus, a readily scalable online behavioral intervention that effectively promotes physical activity in adults with obesity by providing self-efficacy enhancing opportunities may be useful in regard to responding to a global pandemic (i.e., physical inactivity) in an at-risk population (i.e., adults with obesity).

### Activity monitors

Wider use of activity monitors (e.g., pedometers and/or accelerometers) to assess physical activity in field-based research on adults began to be steadily advocated for more than a decade ago [19–22]. A primary reason that the use of activity monitors was advocated for was to address long-standing concerns regarding potential limitations for the validity of physical activity estimates based on self-report [23–26]. Accelerometers generally were recommended in field-based research when the indicator of physical activity was to include a dimension of exercise duration and/or intensity (e.g., time spent in moderate to vigorous physical activity (MVPA)) and the cost of the activity monitor was not prohibitive [19–22]. Recent reports suggest that the use of accelerometers to assess physical activity in field-based research on adults may be increasing [27–29]. The scientific importance of this trend is reinforced by troubling findings that suggest only small to moderate relative agreement and large absolute disagreement between estimates of physical activity based on self-report versus accelerometry [30]. Moreover, there is evidence that even some commercial-grade accelerometers that are relatively modest in cost can provide valid estimates of free-living (i.e., occurring outside of controlled laboratory conditions) physical activity among adults [31].

The use of activity monitors in physical activity behavioral interventions for adults with obesity has been recommended based on two key findings from a recent meta-analysis of 11 randomized controlled trials (RCTs) [32]. The first key finding was that physical activity behavioral interventions with an activity monitor were shown to increase physical activity in adults with obesity. The second key finding was that it appears that adding an activity monitor to an existing physical activity behavioral intervention (previously without an activity monitor) may increase the magnitude of the effect of the intervention on physical activity in adults with obesity. These two key findings, along with a synthesis of 14 relevant RCTs (11 of which were included in the aforementioned meta-analysis), led the Community Preventive Services Task Force to recommend that physical activity interventions for adults with obesity should include activity monitors and behavioral instructions (e.g., web-based education) [33]. Furthermore, the Community Preventive Services Task Force recommends that physical activity interventions for adults with obesity should promote physical activity within a more broadly focused weight management program where there is access to a health care provider [33].

### Feasibility

Assessing the feasibility of participants wearing an accelerometer as requested by the research team for a particular field-based study is recommended [21]. Two large studies conducted in the United States of America (USA) that assessed the feasibility of adult participants wearing an accelerometer as instructed are the 2003–2004 National Health and Nutritional Examination Survey (NHANES) [22] and the 2009–2013 physical activity ancillary study within the Reasons for Geographic and Racial Differences in Stroke (REGARDS) study [34, 35]. While both of these studies provide models for assessing the feasibility of adult participants wearing an accelerometer as requested by the research team, neither of these studies was an online behavioral intervention. The feasibility of participants wearing an accelerometer as requested in a longitudinal online behavioral intervention may pose unique challenges stemming from an inability to hand deliver an accelerometer (as in the 2003–2004 NHANES study) and the lack of an established research-based relationship with participants (as in the 2009–2013 physical activity ancillary REGARDS study).

### Fun For Wellness (FFW)

FFW is an online behavioral intervention designed to promote growth in well-being and physical activity by providing capability-enhancing learning opportunities to participants [36, 37]. The conceptual framework for the FFW intervention is guided by self-efficacy theory [8]. The target audience of the FFW intervention is the adult population who would be comfortable with the online platform within which the intervention is delivered. There is an emerging literature on the efficacy and the effectiveness of the FFW intervention [36–39].

### 2015 FFW efficacy trial

A RCT completed in 2015, hereto forward referred to as the 2015 FFW efficacy trial, provided the initial test of the FFW intervention to promote well-being [36]. Figure 1 depicts the conceptual model that guided the 2015 FFW efficacy trial. The FFW intervention (i.e., engagement with the BET I CAN challenges) was conceptualized as exerting both a positive direct effect and a positive indirect effect through self-efficacy (i.e., well-being self-efficacy), on well-being (i.e., subjective well-being and well-being actions). Each of the constructs depicted in Fig. 1 will be defined in the “Methods” section of this manuscript.

**Fig. 1 Fig1:**
[figure not shown]
The conceptual model that guided the 2015 Fun For Wellness efficacy trial [36]

Data collection for the 2015 FFW efficacy trial occurred within a relatively controlled environment (i.e., adult employees at a major research university in the USA). Results from the 2015 FFW efficacy trial provided some initial evidence for the efficacy of FFW to promote well-being self-efficacy [38]; interpersonal, community, psychological and economic subjective well-being [36]; and interpersonal and physical well-being actions [39]. The protocol for the feasibility study to be described in this manuscript seeks to follow up on the initial evidence provided in the 2015 FFW efficacy trial for the FFW intervention to promote self-reported free-living physical well-being actions (e.g., engagement in physical activity) in adults who comply with the intervention [39].

### 2018 FFW effectiveness trial

A RCT designed to provide an initial evaluation of the effectiveness of the FFW intervention to increase well-being and free-living physical activity in an adult population with obesity enrolled approximately 900 participants and hereto forward is referred to as the 2018 FFW effectiveness trial [37]. Figure 2 depicts the conceptual model that guided the 2018 FFW effectiveness trial. The FFW intervention was conceptualized as exerting both a positive direct effect and a positive indirect effect through self-efficacy, on well-being and physical activity. Four constructs—well-being actions self-efficacy, physical activity self-efficacy, self-efficacy to regulate physical activity, and physical activity—were added to the conceptual model in the 2018 FFW effectiveness trial (i.e., compare Fig. 2 to Fig. 1) based on the findings from the 2015 FFW efficacy trial. Each of the additional constructs in Fig. 2 will be defined in the “Methods” section of this manuscript.

**Fig. 2 Fig2:**
[figure not shown]
The conceptual model that guided the 2018 Fun For Wellness effectiveness trial [37]

The 2018 FFW effectiveness trial was built upon the 2015 FFW efficacy trial by having a stronger focus on promoting physical activity and by recruiting participants from a relatively uncontrolled context (i.e., via an online panel recruitment company) [37]. The increased focus on physical activity in the 2018 FFW effectiveness trial was manifest by a particular emphasis on engaging in a recommended amount of physical activity for health (i.e., time spent in MVPA) in the introduction to the BET I CAN challenges. The 2018 FFW effectiveness trial also was built upon the 2015 FFW efficacy trial by more thoroughly assessing self-reported physical activity with the long form (i.e., 27-items) of the international physical activity questionnaire (IPAQ) [40, 41]. The aforementioned long-standing concerns regarding potential limitations for the validity of physical activity estimates based on self-report, however, are relevant to both the 2015 FFW efficacy trial and the 2018 FFW effectiveness trial. That is, neither the 2015 FFW efficacy trial nor the 2018 FFW effectiveness trial used objective instrumentation (e.g., accelerometry) to measure physical activity.

### Proposed study

The feasibility study proposed in this paper will be the first study to use accelerometry within the FFW online behavioral intervention. The objective of this manuscript is to describe the protocol for a feasibility study designed to address uncertainties regarding the inclusion of accelerometer-based assessment of free-living physical activity within the FFW online intervention among adults with obesity in the USA. Four specific aims will be investigated.

#### Aim 1

To determine if accelerometer-based assessment of physical activity *can* be used within the FFW intervention.

#### Aim 2

To determine if accelerometer-based assessment of physical activity *should* be used within the FFW intervention.

#### Aim 3

To determine *how* to implement accelerometer-based assessment of physical activity within the FFW intervention. Aim 3 assumes a positive response to Aim 2.

#### Aim 4

To provide a preliminary effect size estimate for each direct effect depicted in the conceptual model (see Fig. 2) for the FFW online intervention (e.g., FFW → Physical Activity).

Pursuit of these four specific aims is based on a general conceptual framework for feasibility and pilot studies in preparation for a future definitive RCT [42–44]. Within this conceptual framework, a randomized pilot trial is a type of a feasibility study and a feasibility study may include a focus on the acceptability of an intervention [42–44].

## Methods/design

### Ethical approval

All procedures in this study involving human participants will be in accordance with the ethical standards of the institutional and/or national research committee and with the 1964 Helsinki declaration and its later amendments or comparable ethical standards. The institutional review board at Michigan State University provided necessary permission to conduct this study on 1 April 2019, STUDY00002012. Table 1 provides the SPIRIT flow diagram, which includes a list of the assessments to be taken during the course of this study. A populated SPIRIT checklist is provided in the Additional file 1.

**Table 1 Tab1:** The SPIRIT flow diagram for the Fun For Wellness accelerometer feasibility study

Time point	Study period							
	Enrolment	Allocation	Post-allocation					Close-out
	*−t* _*1*_	0	w1 Weeks 1–3	w2 Weeks 3–7	w3 Weeks 7–13			*t* _*x*_
Enrolment								
Eligibility screen	X							
Informed consent	X							
Allocation		X						
Interventions								
*Fun For Wellness*				X				
*Usual care*			X	X	X			
Assessments								
Gender			X					
Age			X					
Race			X					
Education-level			X					
Marital status			X					
Annual income			X					
Zip code			X					
Height			X	X	X			
Weight			X	X	X			
Physical activity			X	X	X			
Acceptability of accelerometer-based assessment of physical activity			X	X	X			
Self-efficacy to comply			X					
Well-being self-efficacy			X	X	X			
Well-being actions self-efficacy			X	X	X			
Physical activity self-efficacy			X	X	X			
Self-efficacy to regulate physical activity			X	X	X			
Subjective well-being			X	X	X			
Well-being actions			X	X	X			

### Study design

The study design is a prospective, double-blind, parallel group randomized pilot trial. Recruitment of participants is scheduled to begin on 29 April 2019 at a local bariatric services center, hereto forward referred to as the center, within a major healthcare organization in the Midwest of the USA. Eligibility verification and data collection will be conducted online. Three waves of data collection (i.e., at W1, W2, and W3) will be collected over a 13-week period. Figure 3 provides a flow chart for recruitment of participants throughout data collection. Instruments designed to measure demographic information, anthropometric characteristics, acceptability and feasibility of accelerometer-based assessment of physical activity, self-efficacy, and well-being will be included in the study.

**Fig. 3 Fig3:**
[figure not shown]
Flow chart for recruitment of participants throughout data collection

### Recruitment

Participants will be recruited from a relatively controlled local context to allow for the possibility that university-based researchers (i.e., research staff) may need to follow up with participants during the course of the study to address unforeseen areas of uncertainty that often arise during a feasibility study [41–43]. Patients who are candidates for bariatric surgery and are enrolling in the preoperative weight management program provided by the center will be recruited for possible participation in this study. Successful enrollment in the preoperative weight management program provided by the center requires a medical history intake and a physical exam (e.g., medical clearance to engage in physical activity).

Recruitment for possible participation in this study will be extended to each patient near the end of the welcome enrollment visit at the center. At this time, a center staff member will provide the patient with login information to the secure recruitment page on the FFW website which can then be accessed by either a laptop located in the center (and provided by the research staff) or via their own device (e.g., smartphone). The patient will then be asked to independently engage with the FFW website in the waiting room. The center staff member will, however, inform the patient that both they and the research staff are available to respond to any questions that may arise during recruitment and throughout the online pilot study if necessary. Additionally, a member of the research staff may be available in the waiting room (depending on related scheduling issues) to assist the patient with website and/or study-related questions. Research staff will have regular contact with center staff throughout the study to discuss any questions or concerns that may arise.

The recruitment page on the FFW website will provide a brief description of the study and will ask the patient if they are interested in determining if they are eligible for participation in the study. Response options will include “yes”, “no”, and “not now, maybe later” (i.e., “defer”) based on previous research [34]. Patients who select “no” will be invited to provide a brief explanation for their response. Patients who “defer” will be invited to provide a brief explanation for their response and then will be asked if they would like to be contacted again in the future to discuss possible participation in this study. Patients who select “no” or “defer” will be taken to the exit page. The exit page will thank an individual for their time and ask them to check out with center staff. Patients who select “yes” will be asked to create a unique and secure login credential by providing a phone number and an e-mail address and creating a password. Patients who select “yes” will also be asked if research staff can send study-related text messages to the phone number they provided. After the login credential is verified by the patient, the potential participant will be screened to determine their eligibility for participation in the study.

### Eligibility

There are five eligibility criteria for participation in this study. Values for each of the eligibility criteria will be based on self-report by the potential participant. The first two eligibility criteria focus on physical characteristics of the potential participant. The first eligibility criterion is being between 18 and 64 years old. A justification for this criterion is that our target age-based population is adults (i.e., 18–64 years) and not older adults (i.e., 65 years and above) based on evidence-based age groupings for global recommendations on physical activity for health [3, 4]. The second eligibility criterion is a body mass index (BMI) ≥ 25.00 kg/m^2^. The BMI criterion in this study includes overweight (i.e., 25.00–29.99 kg/m^2^) and obese (i.e., ≥ 30.00 kg/m^2^) categories, consistent with many physical activity interventions in adults with obesity [6, 32, 33]. A justification for this criterion is the need to promote physical activity in a BMI-based population in which few individuals may meet public health guidelines for physical activity [5].

The third and the fourth eligibility criteria focus on the interaction of the potential participant and the online intervention. The third eligibility criterion is the ability to access the online intervention. This criterion will be assessed by asking each individual to confirm that they will have access to a technological device (e.g., computer, smartphone) that can access the online intervention via a web browser throughout the study. The fourth eligibility criterion is the absence of simultaneous enrollment in another intervention program promoting either well-being or physical activity. This criterion will be assessed by requiring each individual to confirm that they will not be enrolled in another formal intervention program (not counting the pre-operative weight management program provided by the center) promoting either well-being or physical activity during the FFW study period. A justification for this criterion is a reduction in the likelihood of confounding the results from the current study with results that may be due to enrollment in other programs.

The final eligibility criterion is a willingness to comply with instructions for physical activity monitoring. This criterion will be assessed by asking each potential participant if they are willing to wear an adjustable nylon belt around their waist with two accelerometers attached to it for three 7-day intervals and complete a daily log sheet regarding wear time during each of the three 7-day intervals over a 13-week period. A justification for this criterion is based on the physical activity ancillary REGARDS study where a similar question was asked to potential participants at screening [34]. Individuals who indicate a willingness to comply with instructions for physical activity monitoring will be asked to provide (a) an estimate of their waist circumference for belt sizing and (b) a mailing address where the physical activity monitors can be sent. Individuals who do not meet one or more of the eligibility criteria will be informed that they are ineligible for the study at this time and then will be taken to the exit page.

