Descriptive statistics will be used to determine if accelerometer-based assessment of physical activity *can* be used within the FFW intervention. Threshold values for the traffic light system for each of the specific indicators that will be used to evaluate aim 1 are based on inferences drawn from the results of previous research [22, 34, 46].

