##### Recruitment rate

Recruitment rate will be defined as the percentage of patients who select “yes” when asked if they are interested in determining if they are eligible for participation in this study: (*n*_interested_/[*n*_interested_ + *n*_no_ + *n*_defer_]) × 100. The lower bound threshold is < 40%. The upper bound threshold is ≥ 60%.

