##### Eligibility rate

Eligibility rate will be defined as the percentage of interested patients who are presented with the informed consent form: (*n*_eligible_/*n*_interested_) × 100. The lower bound threshold is < 60%. The upper bound threshold is ≥ 80%.

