##### Consent rate

Consent rate will be defined as the percentage of eligible patients who consent to participate in this study: (*n*_consent_/*n*_eligible_) × 100. The lower bound threshold is < 80%. The upper bound threshold is ≥ 90%.

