##### Participation rates

Participation rate at wave *W*, where *W* = W1 or W2 or W3, will be defined as the percentage of consented patients who provide usable data at wave *W*: (*n*_usable data at wave *W*_/*n*_consent_) × 100. The lower bound threshold is < 50%. The upper bound threshold is ≥ 70%.

The definition of usable data will follow the description previously provided in the *ActiGraph wGT3X-BT* section.

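### Refusal to wear the accelerometers is counted only inside a pooled eligibility rate, so the Aim 1 indicators cannot show how many otherwise eligible patients declined the procedure under test

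*Protocol article*

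**What the plan says.** The Eligibility section lists five criteria. The first four are age, BMI, online access and no concurrent programme. Of the fifth it says: "The final eligibility criterion is a willingness to comply with instructions for physical activity monitoring". It is assessed by asking whether the person will wear a belt with two accelerometers, and keep a daily log, for three 7-day intervals. The consequence of failing any criterion is the same: "Individuals who do not meet one or more of the eligibility criteria will be informed that they are ineligible for the study at this time". The reason given for the fifth is precedent: "A justification for this criterion is based on the physical activity ancillary REGARDS study where a similar question was asked to potential participants at screening".

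Under Data analysis, Aim 1 is to be answered with rates that form a funnel:

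- Recruitment is the share of patients approached who want to be screened, so it comes before the criterion.
- "Eligibility rate will be defined as the percentage of interested patients who are presented with the informed consent form". Red is below 60% and green is 80% or more.
- "Consent rate will be defined as the percentage of eligible patients who consent to participate in this study". Red is below 80% and green is 90% or more.
- Participation at a wave "will be defined as the percentage of consented patients who provide usable data at wave". Red is below 50% and green is 70% or more.
- Retention uses the same consented denominator. Red is below 40% and green is 60% or more.

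Neither Aim 1 nor Table 2 has an indicator for refusal of monitoring at screening.

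**The concern.** A patient who meets the first four criteria but will not wear the belt is a direct negative answer to the Aim 1 question. The plan records that answer as ineligibility, in the same count as a patient who is 65 or who is enrolled in another programme. These exclusions mean different things for a definitive trial. Exclusion for age says nothing about accelerometry, whereas belt refusal is a recruitment cost of accelerometry itself.

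The precedent does not settle how many will refuse. The article's own Feasibility background notes that an online intervention may face particular challenges because it lacks the established relationship with participants that the REGARDS ancillary study had. Willingness is thus one of the uncertainties this pilot is well placed to measure. The limitations in the Discussion treat the criterion only as a matter of honest self-report and do not mention that the later rates come from a pre-selected group.

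What is at stake is interpretation. A set of green lights could be read as feasibility among interested FFW candidates in general, when the later rates show feasibility among those already willing.

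**Working it through.** The plan gives no refusal share and no calculation to reproduce. The check traces the denominators and then asks what the defined rates can identify.

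**Inputs.** The rate definitions come from Data analysis, Aim 1, and the thresholds from Table 2. Let r be the share of patients meeting criteria 1 to 4 who refuse the belt, and o the share of interested patients who fail at least one of criteria 1 to 4. Both are unknown; the values below are assumptions.

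**Step 1: where refusers are counted.** They are in the denominator of the eligibility rate and not in its numerator. They are in neither part of consent (per eligible patient), participation or retention (both per consented patient).

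**Step 2: what the eligibility rate identifies.** Eligibility rate = (1 − o) × (1 − r). With the rate fixed at 80%, o = 1 − 0.80/(1 − r):

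| Assumed r | Implied o | Pooled eligibility rate | Rate on criteria 1 to 4 (1 − o) | Willingness rate (1 − r) |
|---|---|---|---|---|
| 0% | 20.0% | 80%, green | 80.0% | 100% |
| 10% | 11.1% | 80%, green | 88.9% | 90% |
| 20% | 0% | 80%, green | 100% | 80% |

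One observed figure fits all three rows. The last two columns, which the plan does not define, tell them apart. By the same formula with o = 0, refusal can reach 20% with the light still green, and 40% (1 − 0.60) before it turns red.

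**Step 3: what the later rates leave out.** Define overall yield at a wave as the number with usable data divided by the number meeting criteria 1 to 4, that is (1 − r) × consent rate × participation rate. For illustration take consent 90% and participation 70%:

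| Assumed r | Participation rate as defined | Overall yield |
|---|---|---|
| 0% | 70% | 0.90 × 0.70 = 63.0% |
| 5% | 70% | 0.95 × 0.63 = 59.9% |
| 10% | 70% | 0.90 × 0.63 = 56.7% |
| 20% | 70% | 0.80 × 0.63 = 50.4% |

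The reported participation rate is the same in every row. Of the gap between 70% and 50.4% in the last row, 7 points are ordinary non-consent (70 to 63) and 12.6 points are refusal (63 to 50.4).

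**Step 4: scale in this study.** With 30 consented, 90% consent and 80% eligibility, about 30/0.90 = 33.3 are eligible and 33.3/0.80 = 41.7 are interested, so about 8 are screened out. On the defined rates, any number of those 8 could be belt refusers.

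**The case against.** The strongest reply is that refusers are counted. They lower the eligibility rate, which is itself an Aim 1 indicator with a red threshold of 60%. That is right, and a reader who infers that the plan removes refusal from the feasibility question, or that no light responds to it, goes further than the text allows. Refusal is pooled, not discarded. The documents also do not say that refusal is the main way accelerometry would fail.

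Second, the pool may be smaller than it looks. The Discussion notes that the centre's programme requires a BMI of at least 35 or 40, and regards online access as reasonably likely in most cases. That reduces the mixing but does not end it, because age and outside programmes remain. It also means refusal could be a large part of what is left, which strengthens the case for showing it.

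Third, a sequential funnel is ordinary, a study that measures by accelerometer can enrol only people willing to wear one, and a definitive trial that kept the criterion would need these conditional rates. This stands, and is why the criterion itself need not change. It is also why the acceptability items are not part of the point: people who never wore the belt could not answer them.

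Fourth, a reader might infer that lights would turn from green to yellow. The documents do not support this. Such a result comes from placing a rate exactly on its green threshold and assuming a refusal share. It would also apply participation thresholds, defined per consented patient and inferred from previous research, to a different denominator.

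Finally, exclusions by reason may be tabulated in the full protocol or the flow chart, neither of which is visible. That would help, but it would not alter the indicators and denominators the article fixes.

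**Conclusion.** The point holds as one of identification and interpretation. The eligibility light reacts to belt refusal but cannot isolate it: an 80% rate is compatible with 0% to 20% refusal among patients meeting criteria 1 to 4, and refusal of up to 40% can occur without a red light. Both ranges follow from the plan's definitions and thresholds alone; their upper ends are reached when no other exclusion occurs. Consent, participation and retention are conditional on stated willingness, and the article does not say so. The yield figures (63.0% falling to 50.4% as refusal goes from 0% to 20%) rest on assumed refusal, consent and participation. They show the direction and possible size, not an expected result. Nothing here shows that any light would be wrong. It is a worthwhile correction to stated indicators, not a flaw in the criterion or the design.

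**What to change.** Keep willingness as a condition of entry, and change the Aim 1 definitions and Table 2 as follows.

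1. Eligibility rate = number meeting criteria 1 to 4 / number interested.
2. Accelerometer willingness rate = number willing / number meeting criteria 1 to 4, as a new Aim 1 indicator. Its thresholds should be set in advance, and the eligibility thresholds reconsidered, because those in Table 2 were set for the pooled rate.
3. Overall yield at each wave = number with usable data / number meeting criteria 1 to 4, reported descriptively without the participation thresholds. The denominator should be everyone meeting criteria 1 to 4. Consented patients plus refusers would drop willing patients who decline consent (per 100 meeting criteria 1 to 4 with 20% refusal and 90% consent, 50.4/(72 + 20) = 54.8% instead of 50.4%).
4. A sentence stating that consent, participation and retention apply to patients already willing to wear the monitors.

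The cost is small: rewording the definitions and retaining the answers the online screen already asks for, with no extra patients or visits. The downside is one more indicator, estimated in roughly 40 people, and an overall yield that will look less favourable than the participation rate.
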